### CBT + ICT group (cognitive behaviour therapy supported by ICT)

The patients of this group will receive the same interventions as the CBT group, but will receive a reinforcement of the sessions’ content through two different ways, both based on ICTs: a web tool named TEO (Emotional Therapy Online) specially designed to practice the therapeutic strategies at home; and SMS, which will be sent to the patient’s mobile phone with reminders and reinforcements. The software TEO has been designed by the team of psychologists on this project. It is a computer program that is accessed via the internet, aiming to allow participants to continue practicing at home what they have learned in the sessions. For this study, different sessions will be designed and developed. The content of the sessions will be related to the therapeutic components included in the CBT. Patients will access TEO from their homes using a personal password. Besides TEO, messages will be sent through SMS three times a week during the treatment and once a week during the follow-up. The messages will consist of reminders to do their homework, along with reinforcements of the effort made to improve their health.

### Analysis of the barriers for using CBT and ICT in chronic low back pain treatment

This analysis includes 3 groups of patients, resulting from the three experimental conditions, with 8 patients in each, selected by a balanced randomization to ensure variability in gender, age, educational level and the ability to use information and communication technologies. We will apply a focus group strategy that will be accomplished at the end of the therapy. The focus groups will be recorded and analyzed with qualitative analysis methodologies. The clinical staff’s opinion will be obtained using ad-hoc questionnaires.

### Collection and data analysis

Clinical and demographic data will be collected in the clinical interview and from the patient’s electronic health history. In the follow-up, we will collect the data of the questionnaires in the 3rd, 6th and 12th month. Due to the nature of the interventions, it will not be possible to blind the participants. Nevertheless, during the process, the assessors of the results will not know the group of the participants.

The first results will be obtained by intention-to-treat analysis. The time point of the primary objective analysis will be the 12th month, although the previous periods will also be analyzed.

Statistical descriptions will be obtained expressing the continuous variables in mean (standard deviation) or median (quartile) depending on normality or not, the categorical variable by number (percentage) and the 95% confidence interval for each case. Normal distribution will be checked with the Kolmogorov test to determine whether to use parametric or non-parametric tests. To compare continuous variables among the groups, Student’s T-test and Mann-Whitney’s U-test will be used, and for categorical variables, Chi-square or Fisher test, depending on the kind of distribution.

Intra-group changes in the continuous variables along the time points will be explored with Student’s T-test for paired samples. To assess if there are differences among the groups according to pain, disability and the rest of the variables, we will use analysis of covariance (ANCOVA) for each dependent variable. In all the tests, the independent variable will be the group, while the covariate variable will be the basal level of each dependent variable. It will be necessary to have comparable levels of both types of variables to understand correctly the ANCOVA results. Therefore, we will perform different Student’s T test estimations, one for each dependent variable, considering each group as an independent variable in each case. To evaluate whether the changes in the three groups have happened in a different way, we will estimate different ANOVA, an analysis for each dependent variable. In all cases, the independent variable will be the group and time in which the data are collected. In this analysis, we will also study possible interactions. Furthermore, we will evaluate the correlations between the variables using Rho-Pearson and Spearman according to normality. We will also use two multiple linear regression models for pain and disability as dependent variables and in both models, gender, age, pain, catastrophizing, fear avoidance, days taken off at work and time evolution will be employed as independent variables.

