**Methods:**

A randomised controlled trial with 180 CLBP patients recruited from specialised care will be conducted. Participants will be randomly assigned to three conditions: Control group (CG), CBT, and CBT supported by ICTs (CBT + ICT). Participants belonging to the three conditions will receive a conventional rehabilitation program (back school). The CBT group program will last six sessions. The CBT + ICT group will use the internet and SMS to practice the therapeutic strategies between sessions and in the follow-ups at their homes. Primary outcome variables will be self-reported disability and pain intensity. Assessment will be carried out by blinded assessors in five moments: pre-treatment, post-treatment and 3-, 6-, and 12-month follow-ups. The influence of catastrophizing, fear-avoidance beliefs, anxiety and depression in response to treatment in the primary outcomes will also be analysed.

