### Randomization

Participants will be randomly assigned to one of three conditions (Control, CBT and CBT +ICT). Participants will be stratified according to their level of disability: severe (Roland Morris Disability Questionnaire (RMDQ) score > 15), moderate (RMDQ score between 8 and 14) and mild (RMDQ score <7). Allocation will be performed by a computer-generated list according to the degree of disability at baseline. It will be supervised by a statistician not belonging to the research group and unaware of the study characteristics.

During recruitment, the allocation sequence will be concealed. Due to the nature of the interventions, it is not possible to blind the participants. The physiotherapists administering the sessions and the assessors will be unaware of the participants’ allocation. Data analysis will be conducted without being aware of the intervention received by the participants.

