### Sample size

The study has been designed taking into consideration changes of 2 points in the pain intensity measured by the numerical rating scale (NRS) and of 3 points in the RMDS. These changes have been recognised as clinically relevant [35]. According to the results of a previous CLBP sample treated in our health centre, the mean disability according to the RMDS presented a standard deviation of 4, while the mean pain intensity displayed a standard deviation of 2. Considering these data and an alpha of 0.01 and a beta of 0.9 for two-tailed mean tests, the required sample size is 53 to detect changes in disability and 30 to detect changes in pain intensity. Considering an attrition of 15%, the sample will need 60 participants per condition. For further analysis of treatment response according to high or low catastrophizing, fear-avoidance beliefs, depression and anxiety, disability measured by the RMDS will be considered with an alpha of 0.05 and beta of 0.8, resulting in a sample size of 28 participants per group.

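### Baseline disability stratifies the randomisation but is left out of the ANCOVA for pain and all secondary outcomes, which gives up some precision at no gain

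*Protocol article*

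**What the plan says.** - **Randomization.** "Participants will be stratified according to their level of disability", in three RMDQ bands (severe, moderate, mild). "Allocation will be performed by a computer-generated list according to the degree of disability at baseline". The section does not mention blocking or any other means of keeping the arms balanced within a band.
- **Primary outcomes (abstract, Methods).** "Primary outcome variables will be self-reported disability and pain intensity".
- **Collection and data analysis.** For group differences "according to pain, disability and the rest of the variables, we will use analysis of covariance (ANCOVA) for each dependent variable". The model is then fixed for every test: group is the only factor, and "the covariate variable will be the basal level of each dependent variable".
- **Other analyses in the same section.** The t-tests and Mann-Whitney tests carry no covariate. For the repeated-measures ANOVA, "In all cases, the independent variable will be the group and time in which the data are collected". The two regression models for pain and disability list neither treatment group nor RMDQ among their predictors.

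**The concern.** A variable thought important enough to stratify on is normally carried into the analysis model. Here that happens only for disability, where the outcome's own baseline is the stratification variable in continuous form. For pain and for the CSQ, HADS, FABQ, PCS and SF-12, neither RMDQ nor its band enters the ANCOVA, and none of the other listed analyses gives an RMDQ-adjusted treatment effect.

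If baseline disability predicts an outcome beyond that outcome's own baseline, the variation it explains stays in the residual and widens the interval. What is at stake is precision, not bias. This matters most where the expected difference is small, for example between CBT with and without ICT, or where the article gives no sample size, as for all secondary outcomes.

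**Working it through.** **1. The plan's own sample size.** Inputs from the Sample size section: "changes of 2 points in the pain intensity measured by the numerical rating scale (NRS) and of 3 points in the RMDS"; SD 4 (disability) and SD 2 (pain); two-sided alpha 0.01; power 0.90. With n per group = 2(2.576 + 1.282)²(SD/difference)²:
- disability: 2 × 14.88 × (4/3)² = 52.9, so 53;
- pain: 2 × 14.88 × (2/2)² = 29.8, so 30.

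Both stated figures reproduce as plain two-mean comparisons, so the sample size does not rely on any precision from covariates. With 60 per arm and 15% attrition, 60 × 0.85 = 51 per arm are analysed. For a 2-point pain difference, 2/(2√(2/51)) = 5.05, and 5.05 − 2.576 = 2.47, which is power of about 0.99.

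**2. Precision given up.** Let r be the partial correlation between baseline RMDQ and the outcome, given the outcome's own baseline. Adding continuous RMDQ multiplies the residual variance by 1 − r². The interval from the planned model is therefore 1/√(1 − r²) times as wide, and the equivalent sample size is 1/(1 − r²) − 1. The article gives no r, so a range is shown. The last column is the 95% half-width for a pain difference, 1.96 × 2 × √(2/51) = 0.776 points in the planned model (taking the residual SD as 2), divided by the width ratio.

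| Assumed r | Width ratio | Sample-size equivalent | Half-width with RMDQ added |
|---|---|---|---|
| 0 | 1.000 | 0% | 0.776 |
| 0.1 | 1.005 | 1% | 0.772 |
| 0.2 | 1.021 | 4% | 0.761 |
| 0.3 | 1.048 | 10% | 0.741 |
| 0.4 | 1.091 | 19% | 0.711 |

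**3. Are the tests also conservative?** This depends on how allocation is done, so it was simulated: three arms, 153 analysed, outcome SD 2, RMDQ SD 4 with an assumed mean of 12, three bands, 4000 runs per setting. Allocation within bands was either in permuted blocks of six or simple. Results for the planned own-baseline ANCOVA:

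| Partial r | Allocation | Mean model SE | Actual SD of estimate | Rejection rate at nominal 0.05 | Mean SE with continuous RMDQ |
|---|---|---|---|---|---|
| 0.17 | blocked | 0.363 | 0.355 | 0.046 | 0.358 |
| 0.29 | blocked | 0.363 | 0.355 | 0.046 | 0.348 |
| 0.41 | blocked | 0.364 | 0.350 | 0.040 | 0.333 |
| 0.17 | simple | 0.367 | 0.362 | 0.047 | 0.363 |
| 0.29 | simple | 0.366 | 0.362 | 0.049 | 0.352 |
| 0.41 | simple | 0.366 | 0.365 | 0.046 | 0.336 |

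- *Width.* The ratio of planned to adjusted SE is, with blocking, 0.363/0.348 = 1.04 and 0.364/0.333 = 1.09. Without blocking it is 0.366/0.352 = 1.04 and 0.366/0.336 = 1.09. The precision loss in step 2 therefore appears under either allocation method.
- *Overstated SE.* With blocking, the model SE exceeds the actual SD by about 2% (0.363/0.355) to 4% (0.364/0.350). A second set of runs over r = 0.2 to 0.4 gave 1% to 3% and true levels of 0.047 to 0.043. Without blocking, levels were close to nominal in both sets (0.046 to 0.049, and 0.051 to 0.054).
- *Simulation error.* With 4000 runs, a rejection rate near 0.05 has a standard error of √(0.05 × 0.95/4000) = 0.003, so small differences between rows mean little.

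**4. Where precision could matter.** As an illustration only, take a true pain difference of 1 point at alpha 0.01 with 51 per arm. Then 1/(2√(2/51)) = 2.525, and 2.525 − 2.576 = −0.05, giving power of about 0.48. With r = 0.3 and RMDQ added, 2.525 × 1.048 − 2.576 = 0.07, giving about 0.53.

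**The case against.** **The plan is valid as it stands.** ANCOVA on the outcome's own baseline is sound, already removes disability variation shared with that baseline, and errs, if at all, toward caution. The other primary outcome is already adjusted for RMDQ, and pain has ample power at the planned difference. All of this stands, and it limits the point to an efficiency gain.

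**The size rests on a correlation that the article does not give.** This also stands. At r = 0.1 the loss is trivial, and for an outcome unrelated to RMDQ it vanishes. The correlation may differ between pain and each secondary outcome.

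**A condensed article may leave covariates to the full plan.** This carries less weight, because the article names the covariate and applies it to all the tests.

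**A stronger reading that might be inferred.** A reader might conclude that ignoring the stratification makes the standard errors 2% to 9% too large, so that a nominal 5% test runs at about 4.5% down to 3.2% for r = 0.2 to 0.4. Those levels follow from 2[1 − Φ(1.96/√(1 − r²))], which assumes that RMDQ is perfectly balanced as a continuous score. The article does not support that, for two reasons. It states no blocking, and without balance within strata the tests run near their nominal level. Even with blocking, only three coarse bands would be balanced, and the simulated overstatement is about half as large or less. The 4% to 19% sample-size equivalent is what continuous RMDQ would bring as a covariate; it is not power that the stratification has already bought.

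**Conclusion.** The mismatch is explicit: RMDQ governs allocation but is excluded from the ANCOVA for pain and every secondary outcome. The consequence is lost precision in an otherwise valid, unbiased analysis. For assumed partial correlations of 0.1 to 0.4, intervals are about 0.5% to 9% wider than necessary, equivalent to about 1% to 19% of effective sample size; for pain this is at most 0.776 − 0.711 = 0.065 points of half-width.

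Mild conservatism is a conditional addition. If allocation is balanced within strata, standard errors are overstated by roughly 1% to 4%, and a nominal 5% test runs at about 4% to 4.7% for r of 0.2 to 0.4. False-positive rates are not inflated in either case. The planned pain comparison is safe, with 30 per group needed and about 51 analysed. This is a low-severity, free improvement.

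**What to change.** In Collection and data analysis, state that the ANCOVA for pain NRS and for each secondary outcome includes baseline RMDQ as a continuous covariate in addition to the outcome's own baseline. The disability model needs no change.

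The continuous score is preferable to the bands. It recovers more precision (at r = 0.41 with blocking, the SE was 0.333 with the score and 0.342 with band terms). It also avoids the gaps in the stated bands, where scores of 7 and 15 fall in no category.

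The cost is one sentence and one degree of freedom per model. No new data are needed, because RMDQ must be known before a participant can be allocated. Fixing the covariate now also removes any later choice about it.

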### Outcome measures

#### Primary outcomes

**Disability** The Roland-Morris (RM) questionnaire is one of the most widely used measures to assess disability in patients with low back pain [36]. This questionnaire was designed to evaluate low back pain, with 24 statements that describe different daily activities that can be affected by low back pain. The participant has to select the statements that describe the limitations produced by their low back pain. The Spanish version of the RM has shown good psychometric properties (reliability and validity) [37].

**Pain** IMMPACT recommends the use of NRS as a core outcome measure of efficacy in clinical trials of chronic pain treatments [38]. The scale is composed of 11 numbers ranging from 0 to 10, with 0 meaning ‘No pain’ and ‘10’ meaning ‘Pain as bad as you can imagine’. Two different scales will be used, one to assess low back pain and the other to examine sciatica pain.

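### The protocol wrongly makes comparability t-tests a condition for reading the ANCOVA, and leaves open whether a normality pre-test puts an unadjusted test in its place at 12 months

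*Protocol article*

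**What the plan says.** All of this stands in the protocol article under Collection and data analysis, which sets month 12 as the time point of the primary analysis.

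- **Normality rule.** "Normal distribution will be checked with the Kolmogorov test to determine whether to use parametric or non-parametric tests". The next sentence gives the tests: "To compare continuous variables among the groups, Student’s T-test and Mann-Whitney’s U-test will be used". Both are unadjusted, and Mann-Whitney is the only non-parametric test named for comparing a continuous outcome between groups.
- **Model.** For differences among the groups in pain, disability and the other variables, "we will use analysis of covariance (ANCOVA) for each dependent variable", where "the covariate variable will be the basal level of each dependent variable". No condition is attached.
- **Comparability.** "It will be necessary to have comparable levels of both types of variables to understand correctly the ANCOVA results". Then: "Therefore, we will perform different Student’s T test estimations, one for each dependent variable", with group as the independent variable. The sentence does not say at which time point, at which significance level, or what follows from a significant result.

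The section does not say whether the gated tests or the ANCOVA give the primary result, and it names no non-parametric counterpart to ANCOVA.

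**The concern.** Two affirmative rules look wrong.

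First, balance is not needed to read a baseline-adjusted ANCOVA in a randomised trial. Under correct allocation a baseline difference is chance, and the covariate is there to remove its effect. Making the reading depend on comparability tests invites the analyst to doubt the adjusted result just when the adjustment is most useful.

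Second, a normality pre-test decides which family of tests applies, and the non-parametric side has only an unadjusted test. The ANCOVA covers the same outcomes, so there are two prescriptions and no order between them. A choice between them could be made after the data are seen and could differ between the two primary outcomes. The Mann-Whitney test also does not estimate the mean differences on which the sample size rests.

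**Working it through.** **Inputs from the protocol article**
- Sample size: difference 3 points, SD 4 (disability); difference 2 points, SD 2 (pain); two-sided alpha 0.01; power 0.90 (printed as beta); 53 and 30 per group; 15% attrition; 60 per condition.
- Primary outcomes: the 24-item Roland-Morris questionnaire (RMDQ) and pain. For pain, "The scale is composed of 11 numbers ranging from 0 to 10" and "Two different scales will be used, one to assess low back pain and the other to examine sciatica pain". That makes three primary scales, all integer scores.
- Randomization: stratified by RMDQ class.

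**Assumptions (not in the document)**
- Comparability tests at 5%, pairwise between the three arms, 60 per arm.
- Correlation r between baseline and 12-month score of 0.3, 0.5 or 0.7.
- Scores normal apart from rounding to integers within the scale's range.

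**1. The plan's own figure.** n = 2 × (2.576 + 1.282)² × SD² / d².
- Disability: 2 × 14.88 × 16/9 = 52.9, so 53.
- Pain: 2 × 14.88 × 4/4 = 29.8, so 30.

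Both are reproduced. Completers per arm: 60 × 0.85 = 51.

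**2. Why balance is not required.** Given a chance baseline difference D, the unadjusted 12-month difference has expectation (effect + slope × D). ANCOVA subtracts the estimated slope × D. A significant baseline test therefore marks a trial in which the adjustment does more work, not one in which it fails.

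**3. How often the comparability tests would alarm by chance.** Simulated chance of at least one significant result among the three pairwise tests under correct randomisation (20,000 runs):
- one outcome: 12.5%
- two independent outcomes: 22.6%
- three independent outcomes: 32.2%; by arithmetic 1 − (1 − 0.125)³ = 33%

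Correlation between the scales and stratification on RMDQ class lower these figures. At a 1% level the chance is at most 3 × 1% = 3% for one outcome and 9 × 1% = 9% for three.

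**4. How stable the normality verdict is.** Rejection rates for a rounded-normal pain score (SD 2, assumed means 5 to 7):

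| Sample tested | Lilliefors critical values | Uncorrected critical values |
|---|---|---|
| 51 (one arm, completers) | 81–88% | 5–7% |
| 60 (one arm) | 88–94% | 9–10% |
| 153 (pooled, completers) | 100% | 83–94% |
| 180 (pooled) | 100% | 96–100% |

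The protocol fixes neither the version of the test nor whether it is run per arm or pooled.

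**5. Cost if Mann-Whitney displaced ANCOVA.** Approximate power is Φ[d / (SD × √(1 − r²) × √(2/51)) − 2.576], with √(2/51) = 0.198. For Mann-Whitney, set r = 0 and multiply the first term by √0.955 = 0.977.

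Disability, d = 3, SD 4. The unadjusted signal is 3 / (4 × 0.198) = 3.787.
- Mann-Whitney: 3.787 × 0.977 = 3.70; Φ(1.13) = 0.87.
- ANCOVA, r = 0.3: 3.787 / 0.954 = 3.97; Φ(1.39) = 0.92.
- ANCOVA, r = 0.5: 3.787 / 0.866 = 4.37; Φ(1.80) = 0.96.
- ANCOVA, r = 0.7: 3.787 / 0.714 = 5.30; Φ(2.73) = 0.997.

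Simulation with integer scores and t critical values gives slightly lower values: ANCOVA 0.89 / 0.95 / 0.99 against Mann-Whitney 0.84 / 0.85 / 0.86.

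Pain, d = 2, SD 2, r = 0.5: simulated power is 99.7% with ANCOVA and 98.5% with Mann-Whitney.

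**The case against.** The strongest reply is that the ANCOVA is stated without condition for pain and disability, while the Kolmogorov sentence sits in a paragraph on descriptive statistics and simple tests, beside Chi-square and Fisher. On that reading the gate never touches the primary analysis. This is also a condensed article, and an analysis plan that is not shown may settle the order. That stands as far as it goes: the text leaves precedence open and does not say that non-normality replaces ANCOVA.

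Three stronger readings are tempting, and the document does not support them.

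- **The baseline t-tests choose the test.** They do not. They bear on how the ANCOVA is understood, and no switch follows a significant result. That they are baseline tests is itself an inference, though the natural one.
- **The pain scale will go to Mann-Whitney.** It may, under one reading. The normality verdict runs from about 5% to 100% rejection, so certainty is not warranted.
- **The two-stage procedure inflates the type I error.** Simulation does not show this. With no effect, 51 per arm, a rounded pain score and r = 0.5 (8,000 runs, alpha 0.01), gated procedures rejected in 1.12% to 1.16% of runs and ungated ANCOVA in 1.09%, with Monte Carlo error about 0.11%.

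The power argument is also weak for pain: at the planned 2-point difference either test has about 99% power. What remains is that both rules are printed statements, not details left out. The comparability condition is mistaken under any reading.

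**Conclusion.** The point holds in a limited form. The comparability condition is a methodological error. At an assumed 5% level it would raise a false doubt in about 12% of correctly randomised trials for one outcome and in up to about 33% for three independent primary scales, with no stated consequence to guide the analyst. Separately, the section gives two between-group prescriptions for the same outcomes, one of them gated by a pre-test whose verdict on an integer pain scale depends on unstated choices.

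The power cost is conditional on Mann-Whitney actually displacing ANCOVA. For disability at the planned 3-point difference it would be about 85% instead of about 90% to 99%, for assumed correlations of 0.3 to 0.7 with 51 completers per arm and alpha 0.01. That is below the intended 90%. For pain at the planned difference it is about one percentage point. No type I error inflation is claimed. The change should be made, but nothing here invalidates the design.

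**What to change.** In Collection and data analysis:

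- Name ANCOVA, adjusted for the baseline value of the outcome and for the disability stratum, as the single primary 12-month analysis for both primary outcomes.
- Delete the sentence that makes comparable levels a condition for reading the ANCOVA, together with its t-tests. Show baseline balance descriptively by arm.
- Remove the normality gate for outcome comparisons.
- Keep rank-based or bootstrap analyses as sensitivity analyses only.

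If a full analysis plan already fixes the order of analyses, bring its wording into line with this. The cost is analysis wording only: no new data, patients or visits.

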## Methods/design

### Study design

The study will consist of a three-armed (Control, CBT and CBT+ICT) simple-blind randomised controlled trial, with five assessment periods (pre-treatment, post-treatment, and three follow-ups at 3, 6 and 12 months). The study will follow the CONSORT guideline [34].

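### The stated predictor list for the disability regression omits baseline RMDQ, so if the model is fitted to follow-up or change it may mistake severity at entry for an influence on response

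*Protocol article*

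**What the plan says.** The Collection and data analysis section plans "two multiple linear regression models for pain and disability as dependent variables" and gives them a common set of predictors: "in both models, gender, age, pain, catastrophizing, fear avoidance, days taken off at work and time evolution will be employed as independent variables". No disability term and no group term is listed.

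For the group comparison by ANCOVA, the same section says that "the covariate variable will be the basal level of each dependent variable".

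Baseline disability is available. RMDQ is a primary outcome, a pre-treatment assessment is planned (Study design), and the Randomization section states: "Allocation will be performed by a computer-generated list according to the degree of disability at baseline".

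The Abstract (Methods) sets the related aim: "The influence of catastrophizing, fear-avoidance beliefs, anxiety and depression in response to treatment in the primary outcomes will also be analysed". The Background gives it as a secondary objective. The Sample size section mentions a further analysis of response by high or low level of the same four variables.

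**The concern.** In a regression of follow-up disability, the baseline value of disability is normally the strongest single predictor. Without it, the coefficient of any variable that goes with disability at entry picks up part of the entry level. Catastrophizing, fear-avoidance, pain and days off work could all be related to entry disability. A non-zero coefficient would then show that these patients were more disabled to begin with, not that they responded differently.

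The list treats the two outcomes unequally. Because pain is on it, the pain model can contain its own baseline. No reading of the list gives the disability model its own.

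At stake is the interpretation of the secondary analysis: false-positive predictors of response, and more residual variance than the collected data require.

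**Working it through.** **Plan's own figures.** The document gives no figure for the regressions. Its nearest one is 28 per group for the high/low response analysis on disability (alpha 0.05, power 0.8, difference 3, SD 4). It reproduces: 2 × (1.960 + 0.842)² × (4/3)² = 27.9, so 28. It says nothing about covariates.

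**Inputs from the document.** 180 patients and 15% attrition give 180 × 0.85 = 153 completers. The SD of the disability score is 4.

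**Assumed inputs (none is in the document).** Baseline-to-12-month RMDQ correlation ρ = 0.5. Correlations: pain–RMDQ 0.4, fear–RMDQ 0.3, catastrophizing–pain 0.3, catastrophizing–fear 0.4, fear–pain 0.3. Catastrophizing–RMDQ, r, is varied from 0.2 to 0.5. Four unrelated covariates stand for gender, age, days off work and time evolution. Catastrophizing has no effect on 12-month RMDQ once baseline RMDQ is known.

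**Formula.** With standardised variables, 12-month RMDQ = ρ × baseline RMDQ + noise. If baseline RMDQ is left out, the catastrophizing coefficient tends to ρ × g, where g is its coefficient in a regression of baseline RMDQ on pain, fear and catastrophizing. For the correlations above:

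g = (0.91 r − 0.31 × 0.3 − 0.18 × 0.4) / 0.732 = (0.91 r − 0.165) / 0.732.

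The spurious slope in RMDQ points per SD of catastrophizing is 4 × ρ × g. Its standard error on the standardised scale is √[(1 − ρ²R²) × (0.91/0.732) / 145], where R² comes from the same regression and 145 = 153 − 8.

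Worked case r = 0.4: g = 0.199/0.732 = 0.272; coefficient 0.5 × 0.272 = 0.136; R² = 0.255; SE = √(0.936 × 1.243/145) = 0.090; ratio about 1.52. The noncentral t distribution then gives 33% rejection at two-sided 0.05.

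| r | g | Spurious slope (points per SD) | Rejection by formula | Rejection by simulation (4,000 trials) |
|---|---|---|---|---|
| 0.2 | 0.023 | 0.05 | 5% | 4.6% |
| 0.3 | 0.148 | 0.30 | 13% | 13.2% |
| 0.4 | 0.272 | 0.54 | 33% | 32.2% |
| 0.5 | 0.396 | 0.79 | 60% | 60.1% |

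With baseline RMDQ added, the simulated rate is 4.4% to 5.2% in every setting.

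**Sensitivity.**
- At r = 0.4, moving ρ from 0.4 to 0.6 moves the rate from 23% to 46%.
- A smaller model with pain and catastrophizing only has g = (r − 0.12)/0.91. At r = 0.4 and ρ = 0.5 the slope is 4 × 0.5 × 0.308 = 0.62 points and the simulated rate is 46%.
- In that smaller model, a predictor related to RMDQ only through pain (r = 0.4 × 0.3 = 0.12) has g = 0, and the rate stays at about 4% to 6%.
- Over r = 0.3 to 0.5, ρ = 0.3 to 0.7 and N = 153 or 180, the smaller model gives about 10% to 98% for a level outcome and 16% to 91% for a change outcome.

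**Change score.** If the outcome is 12-month minus baseline RMDQ, ρ is replaced by ρ − 1. At ρ = 0.5 the slope has the same size and the opposite sign (−0.54 points at r = 0.4), so patients with high catastrophizing would appear to improve more. Once baseline RMDQ is in the model, the predictor's coefficient is identical for level and change.

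**The case against.** The strongest objection is that the article never calls these regressions the treatment-response analysis. They follow a sentence on correlations. They leave out anxiety and depression, two of the four response variables, and add gender, age and days off work. The only sketch of a response analysis is the high/low comparison in the Sample size section. Time point and outcome form (level or change) are not stated, and time evolution is undefined. If the model describes disability at baseline, baseline RMDQ is the outcome itself and the point falls away. Who will be more disabled later is also a legitimate prognostic question that needs no baseline adjustment.

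This stands, and it makes the point conditional. A reader might infer that the plan will report catastrophizing or fear-avoidance as influencing response on the strength of entry severity alone. The document does not support that: the link to the response objective is an inference from the variables named, and the inflation depends on correlations that it does not give.

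Two further limits also stand. Stratification by RMDQ shows that the variable is available, but it is not itself a reason to include it here, because the regression has no group term. And baseline adjustment alone cannot show that a variable modifies the treatment effect.

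The objection does not remove the omission. The predictor list is stated, so it is not merely a detail left to an unseen analysis plan. Choosing a change score does not rescue the model.

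**Conclusion.** The point holds in conditional form. The stated list leaves baseline RMDQ out of the disability regression, in contrast to the ANCOVA beside it. If the regression is fitted to follow-up or change in disability and read as bearing on response, a predictor related to entry disability beyond what pain and the other listed covariates explain may appear influential when it is not.

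The size rests wholly on the assumed correlations. It runs from no inflation at r = 0.2 to about 60% false positives at r = 0.5 (n = 153, ρ = 0.5), against about 5% with baseline RMDQ included. The direction of the spurious effect depends on whether level or change is modelled, which the article leaves open.

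The primary group comparison by ANCOVA is not affected. The change is worth making because it is almost free, not because a main conclusion is at risk.

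**What to change.** - Add baseline RMDQ as a continuous covariate to the disability regression.
- State that pain in the pain regression is baseline pain, so that each model contains the baseline of its own outcome.
- State the time point of the two regressions and whether the outcome is level or change.
- Describe the coefficients as baseline-adjusted prognostic associations. Without group and group-by-predictor terms they do not show that the treatment effect differs between patients.

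The cost is one degree of freedom and a few words in the analysis section. The data are already collected. Some predictor associations will look weaker.
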